# DECIDE for MOM Provider Training to improve healthcare providers’ competency in engaging and communicating with perinatal individuals: protocol for a non-randomized feasibility study

**DOI:** 10.1186/s40814-026-01857-z

**Published:** 2026-06-03

**Keywords:** Perinatal mental health, Shared decision making, Healthcare provider training, Adaptation of evidence-based practice, Dissemination and implementation, Health systems

## Abstract

**Background:**

Appropriate perinatal mental health care is an important public health concern as mental health disorders are common pregnancy complications. Perinatal and mental health care providers’ competencies in meeting mental health needs of perinatal individuals can increase access to appropriate mental health care. Despite the importance, perinatal and mental health care providers report discomfort in treating perinatal individuals with mental health needs due to the lack of evidence-based guidance for mental health treatment decisions, differences in beliefs and attitudes, and concerns about adverse effects on mental health and pregnancy outcomes. The proposed study aims to adapt the DECIDE provider training to improve care providers’ competencies in effectively engaging and communicating with perinatal individuals for shared decision making across pregnancy and postpartum stages in perinatal care settings. DECIDE stands for Decide the problem; Explore the questions; Closed or open-ended questions; Identify the who, why, or how of the problem; Direct questions to your health care professional; Enjoy a shared solution.

**Methods:**

The proposed study with a single-arm prospective design will make content adaptation (i.e., adding topical training content to fit perinatal mental health care) and process adaptation (i.e., creating asynchronous training modules to reduce the burden for care providers) to the DECIDE provider training. The acceptability, appropriateness, and usability of adapted DECIDE provider training for wide dissemination and rapid implementation in health systems will be assessed.

**Discussion:**

DECIDE teaches healthcare providers skills for perspective-taking, reducing attributional errors, and increasing receptivity to the client population. An adapted DECIDE provider training is expected to be an effective guiding tool for perinatal and mental health providers in delivering competent care for perinatal individuals with mental health disorders. This study will determine the acceptability, appropriateness, and usability of the adapted DECIDE provider training to support high quality perinatal mental health care delivery.

**Trial registration:**

ClinicalTrials.gov NCT07098260. Registered on 17 August 2025. https://clinicaltrials.gov/study/NCT07098260

## Introduction

Appropriate training for healthcare providers to meet unique mental health needs of perinatal individuals is an important public health concern. Mental health disorders among perinatal individuals are common pregnancy complications in the USA with 13% of perinatal individuals experiencing depression after childbirth and 43% of depressed perinatal individuals experiencing co-occurring anxiety [1]. Kang-Yi and colleagues’ research [2] found that over 80% and nearly 40% of low-income pregnant women with psychiatric disorders in one of the largest states in the USA drop out of psychotropic medication use and psychotherapy, respectively, early in their pregnancy. Despite the importance of appropriate perinatal mental health training, there is a lack of opportunities for structured training designed for healthcare providers such as psychiatrists, psychologists, counselors, psychiatric nurse practitioners, and other non-psychiatric providers such as midwives and obstetrics and gynecology clinicians who provide care for perinatal individuals with mental health needs [3–5]. These care providers report the difficulty of treating pregnant and postpartum women with mental health disorders due to the lack of evidence-based guidance for mental health treatment decisions during pregnancy, differences in beliefs and attitudes for diverse populations, and concerns about adverse effects on perinatal individuals such as self-harm and suicide [4, 6, 7].

Effective engagement and communication with perinatal individuals are essential competencies required for healthcare providers to successfully meet the unique mental health needs of perinatal individuals across pregnancy and postpartum stages in perinatal and mental health care settings [8, 9]. DECIDE is an evidence-based shared decision making intervention developed to improve shared decision making in behavioral health care through effective engagement and communication with patients with mental illness [10]. DECIDE stands for Decide the problem; Explore the questions; Closed or open-ended questions; Identify the who, why, or how of the problem; Direct questions to your health care professional; Enjoy a shared solution [10]. DECIDE provider training teaches healthcare providers skills for perspective-taking, reducing attributional errors, and increasing receptivity to the client population in shared decision making [10–13]. DECIDE including DECIDE-Patient Activation and DECIDE clinician intervention has demonstrated the effectiveness in improving patient activation [10, 14], patient self-management [12, 14], perceived quality of care [12], collaborative decision-making [10], and anxiety symptoms [13] when implemented in outpatient mental health care for adults. The DECIDE implementation in children’s behavioral healthcare setting has identified the need for adaptations of DECIDE to fit target populations and care settings [15].

## Methods

### Aim and objectives

This study aims to (1) make content adaptation (i.e., adding topical training content to fit perinatal mental health care) and process adaptation (i.e., creating asynchronous training modules to reduce the burden for care providers) to the DECIDE provider training and (2) assess the acceptability, appropriateness, and usability of adapted DECIDE provider training for wide dissemination and rapid implementation of DECIDE in maternal mental health care delivery. This study is approved by the Rutgers University Institutional Review Board.

### Study design

The study involves two phases.

#### Phase 1: Adapt DECIDE to translate the knowledge of DECIDE provider training into perinatal mental health care

The investigators will use Iterative Decision-Making for the Evaluation of Adaptations (IDEA) [16] and the Framework for Reporting Adaptations and Modifications-Enhanced (FRAME) [17] as guiding frameworks for the adaptation. Agency for Healthcare Research and Quality’s synthesis of research evidence for pharmacologic and nonpharmacologic treatments for maternal mental health care [18] will be used as the guiding tool for selecting the key questions for shared decision making. The example questions include the following: whether to offer nonpharmacologic interventions alone or in combination with pharmacologic intervention for specific perinatal mental health conditions and which nonpharmacologic interventions for perinatal mental health lead to optimal patient outcomes. The core content of the DECIDE provider training [10, 19] will be retained in a two-hour asynchronous training. The five modules include shared decision-making, perspective-taking (understanding perinatal individuals’ circumstances and perceptions), patient activation, attributional errors, and being a responsive provider to perinatal individuals. Clinical illustrations will be created to address patient and provider concerns for perinatal mental health, such as pharmacological mental health treatment in relation to breastfeeding, pregnancy complications, maternal harms and child outcomes, patient sociodemographic factors, mental illness and prior pregnancy history, and patient preferences.

*Stakeholder engagement to adapt DECIDE provider training*: The investigators will establish a provider advisory board composed of perinatal and mental health care providers and recruit subject matter experts with expertise in perinatal mental health care, shared decision making, and health systems.

*Recruitment of provider advisory board*: The investigators will recruit five provider advisory board members to guide adaptations to DECIDE provider training. The members will include those who provide perinatal mental health care such as nurses, psychologists, social workers, midwives, counselors, peer specialists, and other providers. The advisory board will help identify content adaptations to be made to fit mental health treatment for perinatal individuals, review asynchronous training modules and clinical illustrations, provide feedback on the provider training materials for revisions to be made, and advise how to best implement the adapted DECIDE provider training in health systems.

*Recruitment of subject matter experts*: The investigators will recruit three subject matter experts with expertise in perinatal mental health, physical and emotional well-being, symptom management, shared decision making, and health systems. The experts will guide key content adaptations to be made to the provider training modules, provide relevant resources to create the content adaptation, co-develop scripts for the training vignettes for clinical illustrations, and review provider training materials and make recommendations.

Focus groups will be conducted with the advisory board and subject matter experts to develop content adaptation and strategies for rapid implementation and wide dissemination of the DECIDE provider training in health systems. The focus groups will be held on a secure Health Insurance Portability and Accountability (HIPAA)-compliant Zoom. Focus groups through Zoom have been reported to be an excellent method for programming and managing focus groups [20, 21]. A semi-structured topic guide consisting of broad, open-ended questions will include questions for structured stakeholder consultation/discussion: (1) What are the anticipated key facilitators and barriers to using DECIDE as a shared decision making tool in health systems? (2) What are the components that must be included or avoided in the adaptations to the DECIDE provider training to ensure that perinatal and mental health providers in health systems use DECIDE skills taught? and (3) What are appropriate and acceptable strategies to integrate the adapted DECIDE provider training into routine perinatal care processes?

*Create, record, edit, and upload the adapted DECIDE provider training in Canvas*: Gathering stakeholders’ input, the investigators will adapt training content, develop scripts for vignettes, revise the training content and scripts through the iterative process of reviews and revisions by engaging the provider advisory board and the subject matter experts, and record training modules in Zoom webinars. Video clips for clinical illustrations created based on the scripts will be inserted into the adapted DECIDE provider training. This recorded asynchronous training will be edited and uploaded in a Canvas course.

#### Phase 2: Assess the acceptability, appropriateness, and usability of the adapted DECIDE provider training to build new knowledge of DECIDE implementation in perinatal mental health practice

The study will recruit 35 perinatal and mental health providers, including midwives, primary care doctors and nurses, social workers, psychologists, case managers, counselors, peer specialists, and obstetrics and gynecology care providers who provide mental health care to perinatal individuals within health systems. Health systems include hospitals and other healthcare organizations (e.g., home visit programs, state medical assistance and health services programs, federally qualified health centers).

##### Sample size justification

The primary aim of the study is to evaluate the feasibility and acceptability of adapted training, including recruitment, retention, training engagement, and data collection processes, rather than conduct hypothesis testing or establish efficacy. Following guidelines for sample sizes for feasibility studies [22, 23] for sufficient estimates of key feasibility parameters, the current study aims to recruit 35 participants, which is considered adequate for assessing feasibility outcomes and estimating variability in outcome measures.

Inclusion criteria:Perinatal or mental health care providers who currently provide perinatal mental health care within health systemsAges between 18 and 64Must be able to understand the training content in English and comfortably complete the assessments and share feedback in English

Exclusion criteria:Healthcare providers who do not practice as part of a health care systemHealthcare providers who do not practice in the USAHealthcare providers who do not currently provide perinatal mental health care

The study will identify potential health systems that will implement adapted DECIDE provider training. Eligible participants in the health systems will receive an email invitation that includes participation information. Health system leaders reached out by the study team will help recruit by disseminating the training information and encouraging their clinicians to take the training. For participants interested in taking part, a study team member will email further information about the study, obtain electronic consent, collect baseline data, and offer instructions for taking the asynchronous online training.

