### Criteria for feasibility

*Intervention uptake and engagement*: 80% or more registered participants logging in to the DECIDE for MOM Provider Training.

*Acceptability, Feasibility, and Appropriateness*: 3 (which indicates moderate agreement) or higher AFAS subscale mean scores for acceptability, feasibility and appropriateness at both immediately after the training and one-month follow-up assessments. Qualitative data collected through open-ended questions of the assessments and focus groups will be used to gain in-depth insights into perceived acceptability, appropriateness, usability including facilitators and barriers, and strategies for wide dissemination and rapid implementation of the adapted training in the real-world setting.

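### The primary aim names recruitment, retention and data collection, but the feasibility criteria test only login and AFAS means, so all of them can be met with most participants lost

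*Protocol article*

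**What the plan says.** All places are in the protocol article.

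- **Sample size justification.** The primary aim covers "feasibility and acceptability of adapted training, including recruitment, retention, training engagement, and data collection processes". The study is framed as one of estimation, "rather than conduct hypothesis testing or establish efficacy". The size rests on this aim. Its stated basis is "Following guidelines for sample sizes for feasibility studies [22, 23] for sufficient estimates of key feasibility parameters", and on that footing "the current study aims to recruit 35 participants".
- **Aim and objectives.** The second aim is to "assess the acceptability, appropriateness, and usability of adapted DECIDE provider training for wide dissemination and rapid implementation". Recruitment, retention, engagement and data collection are not named.
- **Criteria for feasibility.** There are two numerical criteria. For uptake and engagement it is "80% or more registered participants logging in to the DECIDE for MOM Provider Training". For the AFAS, the mean of each of the three subscales must reach 3 on the 1 to 5 scale, both immediately after training and at one month. Qualitative data add insight but carry no threshold.
- **Outcome measures.** Only providers who finish the training are asked for the one-month assessment.
- **Participant recruitment and retention.** A weekly log, email reminders and gift cards support retention. The $100 card depends on all five modules and both online assessments. No retention rate or target is given.

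**The concern.** The article states its aim in two ways, and the criteria match neither fully. Of the four processes in the primary aim, login covers one (training engagement), and only in a minimal form. The other three have no criterion by which the study is judged feasible.

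The AFAS criterion does not fill the gap. It is a mean over whoever answers, with no floor on how many do. At one month it is also restricted to those who completed the training, so people who dropped out, perhaps because the training did not suit them, cannot lower it. The study could therefore meet all its criteria while losing most of its participants. Retention and follow-up completion are what the planners of the larger evaluation mentioned in the Discussion would need to know, and a standard chosen after the data are seen would carry little weight.

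**Working it through.** **The plan's own figure.** The 35 cannot be reproduced, because the section gives no target rate, precision or dropout and cites guidelines instead. Nothing here challenges it.

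**Aim against criteria**

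| Named in the primary aim | Numerical feasibility criterion |
|---|---|
| Acceptability | AFAS mean of 3 or higher |
| Training engagement | Login by at least 80% of registered participants |
| Recruitment | None (35 is a target outside the criteria) |
| Retention | None |
| Data collection | None |

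**Applying the criteria to 35 participants.** Assume all 35 who consent count as registered.

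1. Login: 0.80 × 35 = 28, so 28 logins meet the criterion whatever happens afterwards. The denominator is those registered, so 16 of 20 (80%) would also pass if only 20 were recruited.
2. Suppose 12 answer at one month and the subscale means are 3.2 at both assessments (assumed). Retention is 12/35 = 34.3% and loss is 23/35 = 65.7%. Both criteria are met.
3. Can the respondents' mean mislead? Take the 28 who logged in. The 12 respondents contribute 12 × 3.2 = 38.4. A mean of 3 over 28 needs 28 × 3 = 84. The 16 who did not answer would have to average (84 − 38.4)/16 = 2.85. If they would have scored below 2.85, the mean over everyone who started is under the threshold, yet the study passes.
4. A more extreme case, also with assumed scores: 10 respondents at 3.5, and 25 lost who would have averaged 2.0, give (10 × 3.5 + 25 × 2.0)/35 = 85/35 = 2.43 over all 35. The criterion is still met.

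**What a completion criterion would do.** With X the number of 35 completing, X ~ Binomial(35, p). The rule is met with probability P(X ≥ r). The thresholds are illustrations, not values from the article.

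| Rule | r | Observed rate at r (exact 95% CI) | p = 0.60 | p = 0.70 | p = 0.80 |
|---|---|---|---|---|---|
| At least 80% | 28 | 80.0% (63.1% to 91.6%) | 0.010 | 0.133 | 0.599 |
| At least 70% | 25 (0.70 × 35 = 24.5) | 71.4% (53.7% to 85.4%) | 0.112 | 0.510 | 0.925 |

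At p = 0.90 the 80% rule is met with probability 0.980. At p = 0.50 the 70% rule is met with probability 0.008. Either rule would almost always reject retention of 50% or less, which the present criteria allow.

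**The case against.** The strongest reply is that this is a small single-arm study set up to estimate, with its emphasis on qualitative data. The aim says evaluate, and retention can be evaluated descriptively without a threshold. Recruitment does have a number, 35. Payment tied to all modules and both assessments makes heavy loss less likely. A condensed article may also leave detail to the full protocol or analysis plan.

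Part of this stands. The loss of 66% is a chosen case that shows what the rule permits; it is not a forecast. Descriptive reporting of retention remains possible. But the article has a section devoted to feasibility criteria, with numerical thresholds, so the mismatch lies in what it fixes and not in what it omits for brevity. Reminders, a log and gift cards are procedures, not standards.

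Two stronger readings are tempting and should not be adopted:

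- A reader might infer from "Health system leaders reached out by the study team will help recruit by disseminating the training information" that the number invited, and so the recruitment rate, cannot be known. The same section says eligible providers receive an email invitation. It does not say who sends the invitations or whether they are counted. Not stated is not the same as unknown.
- A reader might infer a formal stop-or-proceed decision resting on these two criteria. The article states no such rule. The Discussion says only that the findings will inform a later large-scale evaluation if appropriate.

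**Conclusion.** The concern holds as a mismatch between the stated primary aim, the listed aims and the feasibility criteria. Three of the four processes in the primary aim have no criterion, and the AFAS means have no minimum response behind them. All stated criteria can be met with 28/35 logging in and 12/35 (34%) answering at one month, so the rule as written can support a wrong conclusion on feasibility.

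The example assumes that 35 are registered and that the respondents' means are 3.2. How far the means could mislead depends on what those lost would have scored, which is unknown. The structural gap needs none of these assumptions. The point should be fixed. It does not threaten participants, the sample size or the design, and a change of wording can resolve it.

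**What to change.** Bring Aim and objectives, Sample size justification and Criteria for feasibility into line, in one of two ways.

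**Add the missing criteria.**
- Prespecify, with all consented participants as denominator, a criterion for completing the five modules and for completing both the immediate and the one-month assessment.
- Report each AFAS mean with its number of respondents and the percentage of consented participants they represent.
- Judge recruitment against the stated target of 35.

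The cut-off is for the sponsor to choose and justify. An 80% rule (28/35) mirrors the login benchmark, but at a true rate of exactly 80% it fails about 40% of the time (1 − 0.599). A 70% rule (25/35) then fails about 7% of the time (1 − 0.925), but passes about half the time at a true rate of 70%.

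**Or narrow the aim** in Sample size justification to what the criteria test, and describe recruitment, retention and data collection as reported descriptively without a standard.

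**Cost.** Either route needs a protocol modification approved by the institutional review board, and a registry update if the record carries the same text. Module and assessment completion must be known anyway to pay the $100 gift card, so no new assessment is needed. Under the first route the study can fail on retention, which is the purpose of adding the criterion.

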### Intervention

Participants will take an asynchronous online DECIDE for MOM Provider Training, the adapted version of DECIDE provider training. The training will take approximately 2 h. The original core content of the DECIDE provider training [10], will be kept while clinical illustrations will be adapted to fit perinatal care settings. The five modules of the adapted DECIDE Provider Training will include shared decision-making, perspective-taking, patient activation, attributional errors, and being a responsive provider to perinatal individuals. Table 1 shows the participant enrollment, intervention and assessment timeline.

**Table 1 Tab1:**
[figure not shown]
Participant Timeline: Schedule of Enrollment, Intervention, and Assessments

Note: SPRIT (Standard Protocol Items: Recommendations for Interventional Trials) template used for the report [24]

### Outcome measures

To identify the acceptability, appropriateness, and usability of adapted DECIDE provider training, the Acceptability, Feasibility, and Appropriateness Scale (AFAS) [25] developed for the assessment of implementation outcomes for training in evidence-based practices will be used. The measure has demonstrated a good fit to the hypothesized three-factor structures (RMSEA = 0.058, CFI = 0.990, TLI = 0.987) and acceptable internal consistency (α = 0.86 to 0.91). The AFAS uses a 5-point Likert scale with 1 indicating “not at all” and 5 indicating “extremely.” A few examples of the items are: “To what extent are you satisfied with the training you received and the practices covered?”, “How comfortable are you with the practices contained within the training?”, “How well do the information and practices fit with your overall approach to service delivery and the setting in which you provide care?” AFAS has demonstrated sensitivity to assessing workshop-specific perceptions about training acceptability and feasibility [25].

Open-ended questions will be added to obtain detailed information on user acceptability, appropriateness and usability. The example questions include the following: (1) Share your experience of taking the asynchronous online training regarding login, course navigation, module organization, and other aspects of accessing the training (2) Did the training change how you interact with perinatal individuals with mental health disorders? What are the specific examples? (3) What are the best strategies to effectively implement the DECIDE for MOM Provider Training within your organization?

The online assessment of acceptability, appropriateness, and usability will be conducted immediately after and one month after the training. Considering that immediately measuring acceptability, appropriateness, and usability can increase the correlation between appropriateness and usability but less highly correlated post-implementation of an intervention as providers perceive usability differently once they actually use the skills taught, [26] providers who complete the training will be asked to also participate in the one-month follow-up assessment.

Focus groups with the training participants will be conducted to gain an in-depth understanding of participants’ perceptions of acceptability, appropriateness, and usability of the adapted DECIDE provider training and thoughts about strategies to promote high-quality implementation of the training. The focus group meetings will be held on a secure HIPAA-compliant Zoom. The semi-structured topic guide will be used for structured stakeholder consultation/discussion: (1) What are the key facilitators and barriers to practicing DECIDE skills taught in perinatal mental health care? (2) What are the components that must be included or avoided in the DECIDE provider training to ensure that mental health providers in health systems use it as a shared decision making tool? and (3) What are appropriate and acceptable strategies to implement the DECIDE Provider Training as part of the routine perinatal mental health care at participants’ organization?

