### Participant recruitment and retention

Thirty-five perinatal and mental health care providers who meet the inclusion and exclusion criteria will be recruited as participants for the training. A study team member will provide initial instructions for training course login and communicate with participants for technical issues via email. The study team will keep weekly participant log to support participant engagement and retention. Training and online assessment completion and focus group participation will be encouraged through email reminders. Participants will receive a $100 e-gift card for completing all five modules of the training and two online assessments and an additional $50 e-gift card for participating in a focus group and sharing in-depth feedback about the training, experience of using the DECIDE skills, and strategies for implementing the training as part of routine perinatal care in health systems.

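### The AFAS success rule rests on providers who finish the training, and the only other criterion counts log-ins, so both can be met despite heavy attrition

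*Protocol article*

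**What the plan says.** All references are to the Protocol article.

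- **Who rates, and when (Outcome measures).** The online assessment of acceptability, appropriateness and usability "will be conducted immediately after and one month after the training". For the second occasion the text adds that "providers who complete the training will be asked to also participate in the one-month follow-up assessment". The open-ended questions, which cover log-in, navigation and module organization, are added to the AFAS.
- **What is paid for (Participant recruitment and retention).** "Participants will receive a $100 e-gift card for completing all five modules of the training and two online assessments". There is "an additional $50 e-gift card for participating in a focus group". No part payment is described.
- **What counts as success (Criteria for feasibility).** There are two rules. At least 80% of registered participants must log in. And the results must show 3 "or higher AFAS subscale mean scores for acceptability, feasibility and appropriateness", at both assessments. The second rule has no stated denominator and no minimum number of raters.
- **What the study is for (Sample size justification).** The primary aim is feasibility and acceptability, "including recruitment, retention, training engagement, and data collection processes", "rather than conduct hypothesis testing or establish efficacy". The target is 35 providers.

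**The concern.** The AFAS is meant to show whether providers find the training acceptable, feasible and appropriate. Stopping a course of about two hours partway can itself be a sign that it was not. Yet the plan describes no point at which such a provider would be asked. The log-in rule does not fill the gap: it is met once a provider opens the course, whatever happens next. Neither rule covers module completion or response to the assessments, although retention, engagement and data collection are named in the primary aim.

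At stake is the reading of a pass. The result is intended to support wide dissemination and to inform a larger evaluation. A pass based on a minority of participants would look the same, under these criteria, as a pass based on nearly all of them. Ratings and reasons for stopping that were never requested cannot be recovered afterwards.

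**Working it through.** **Inputs from the article.** N = 35. Log-in threshold: 0.80 × 35 = 28. AFAS range 1 to 5; pass mark 3 on each subscale mean, at both times. The article gives no expected completion rate, AFAS mean or standard deviation, and the 35 has no formula behind it, so there is no planned figure to reproduce.

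**Assumed for illustration.** Raters' mean m mostly 3.5; number of raters c from 14 to 28; mean that non-raters would have given, x, from 1 to 2.5.

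**Step 1: can both rules be met with heavy attrition?** Suppose 28 log in, and 14 of them finish and rate at 3.5. Log-in: 28/35 = 80%, met. AFAS: 3.5 ≥ 3, met. The ratings come from 14/35 = 40% of those enrolled and 14/28 = 50% of those who logged in.

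**Step 2: when would the missing ratings change the AFAS result?** The mean over a base of B people is (c·m + (B − c)·x)/B. It falls below 3 when x is below (3B − c·m)/(B − c).

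Base: all 35 enrolled, m = 3.5.

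| Raters c | Break-even x | Mean if x = 1 | x = 2 | x = 2.5 |
|---|---|---|---|---|
| 28 | 1.00 | 3.00 | 3.20 | 3.30 |
| 24 | 1.91 | 2.71 | 3.03 | 3.19 |
| 21 | 2.25 | 2.50 | 2.90 | 3.10 |
| 18 | 2.47 | 2.29 | 2.77 | 3.01 |
| 14 | 2.67 | 2.00 | 2.60 | 2.90 |

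Worked line: c = 21 gives (3 × 35 − 21 × 3.5)/14 = (105 − 73.5)/14 = 2.25. For c = 28 the worst case is (28 × 3.5 + 7 × 1)/35 = 105/35 = 3.00.

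Base: the 28 who logged in, m = 3.5.

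| Raters c | Break-even x | Mean if x = 1 | x = 2 | x = 2.5 |
|---|---|---|---|---|
| 24 | below 1 (cannot fail) | 3.14 | 3.29 | 3.36 |
| 21 | 1.50 | 2.875 | 3.125 | 3.25 |
| 18 | 2.10 | 2.61 | 2.96 | 3.14 |
| 14 | 2.50 | 2.25 | 2.75 | 3.00 |

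**Step 3: dependence on the raters' own mean (base 35).** With 28 raters at 3.2 the break-even is (105 − 89.6)/7 = 2.2, so even modest attrition matters near the pass mark. With 24 raters at 4.0 the worst case is (96 + 11 × 1)/35 = 3.06, so the result is safe.

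**The case against.** A reader might infer that the criteria are judged on satisfied survivors and that the means are biased upward. The document does not support either as a fact. Busy clinicians may stop for lack of time, and nothing links stopping to low ratings. Direction and size depend on completion rates and scores that are not given.

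A reader might also infer that the $100 condition worsens the selection. It cuts both ways. A non-completer has no paid reason to rate, but a dissatisfied provider has a paid reason to finish and give low scores. Email reminders and a weekly participant log push the same way.

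Other points stand in part:

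- The explicit restriction covers the one-month assessment only. For the immediate one it follows from the timing. The content of Table 1, the assessment schedule, was not available for this review, so the timing rests on the text.
- The follow-up has a stated purpose, to capture views once the skills have been used. Someone who saw one module is poorly placed to rate the whole training. This supports reporting partial exposure separately; it does not support leaving those people unasked.
- It would be too strong to say that barriers to completion go unrecorded. The focus groups are with training participants and do not exclude non-completers. However, the listed topics concern practising the skills, content and implementation, not reasons for stopping.
- Reversal is not inevitable. With raters at 3.5 and non-raters at 2.2, 21 raters give (73.5 + 30.8)/35 = 2.98, but 22 give (77 + 28.6)/35 = 3.02.
- The AFAS rule is a descriptive cut-off in a feasibility study, not a test. It is nevertheless the stated basis for calling the training acceptable.

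**Conclusion.** The point holds in a limited form. As written, the AFAS rule rests on completers who respond: expressly at one month, by implication immediately after training. The log-in rule does not offset this, so both can be met with ratings from as few as 14 of 35 in the example above.

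Whether that makes the means too favourable is conditional on non-completers rating lower. Under the assumed raters' mean of 3.5, the conclusion over all 35 reverses with 21 raters if the other 14 would average under 2.25, and cannot reverse with 28 raters. High completion or ratings well above 3 would make the issue harmless. Low completion with ratings near 3 would make the pass uninterpretable. The plan should be able to tell these cases apart, and at present its criteria do not.

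**What to change.** **In Outcome measures.** Send the AFAS and the open-ended items to everyone who logged in at least once. For those who do not finish, trigger them at a fixed time after course access, and add one item on the reason for stopping.

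**In Criteria for feasibility.** Report each AFAS mean with the number of raters out of those logged in and out of those enrolled, and report module completion beside it. Add a sensitivity analysis that gives logged-in non-raters a stated range of low scores, for example 1 to 2.5, and shows whether each mean stays at 3 or above. Keep participants who never log in under the uptake criterion: they have no experience of the training to rate, and counting them merely as below 3 would not define a value for a mean.

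**Payment.** Separating payment for the ratings from module completion is optional. It would encourage non-completers to respond but weaken the incentive to finish, so it is a trade-off for the investigators.

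**Cost.** An IRB modification, revised wording and survey triggers. Some ratings will come from people who saw only part of the training; these should be shown separately as well as pooled. The change is best made before data collection, or by prompt amendment if it has begun.
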